### Patient questionnaires

Patients who wish to participate with questionnaires are requested to fill in a questionnaire immediately after the initial GP consultation and after four, eight, and 52 weeks. In case the patient does not respond to a questionnaire, reminders are sent following one- and two-week delays. In the first questionnaire, patients are asked for baseline characteristics on educational level, co-morbidity, as well as the STarT Back Tool questions. Included in the first questionnaire and repeated in the next three questionnaires are questions on the secondary outcomes and about advice received and advice followed.

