### Data completeness, quality, and security

Every fortnight, the study group will perform evaluations of the number of included patients, as well as completion and accuracy of data forms, and act on any problems (missing data, slow inclusion, etc.). Data completeness regarding referral to secondary care treatment (primary outcome) is expected to be between 98 and 100%. Data completeness from patient questionnaires (secondary outcomes) is expected to be about 80%. Paper-version questionnaires will be double keyed into the database. Pop-up data are sent daily to the DAMD database, and from the DAMD to the project database on a weekly basis. The project database is provided with access login and writing recording. Backup copying will be performed daily.

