### Secondary outcomes

Changes from baseline to four, eight, and 52 weeks are evaluated for the following secondary outcomes: physical function, evaluated by the 23-questionnaire Roland Morris Patrick (for the individual patient, a three-point improvement is considered clinically relevant); pain score, evaluated by a numerical rating scale from 'no pain’ to 'maximal pain’ (score 0 to 10; a 30% change is considered clinically relevant for an individual patient); health-related quality of life, evaluated by EQ-5D score; patient satisfaction (treatment; a 30% change is considered clinically relevant for an individual patient); patient satisfaction (outcome; a 30% change is considered clinically relevant for an individual patient); employment status (have work, yes/no); and sick leave (number of days).

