### Statistics

Analyses will be performed according to the CONSORT guidelines [19]. Data will be analysed according to the intention-to-treat principle. We will obtain descriptive statistics for process measures; baseline characteristics and outcome measures will be presented as mean (*SD*) or numbers (%) with 95% confidence intervals, if normally distributed, or otherwise as medians (quartiles). A Generalised Estimating Equation model with logit link and exchangeable correlation will be carried out. Primary outcome (12-week referral rates) will be analysed in logistic regression models and with respect to provider number cluster effects. Employment status will be analysed by logistic regression models. The other secondary outcomes (Roland Morris Questionnaire, numerical pain rating, EQ-5D, patient satisfaction, and sick leave) will be analysed with practice number as a random effect in a linear mixed effects model with provider number as the intercept in profile analyses.

Primary exposure is allocation group (intervention or control group) stratified by the size of the practices. Following practice number, related baseline variables will be analysed and possibly adjusted for size of practice (≤2,000, 2,001 to 5,000, >5,000 listed patients), urbanity, and degree of received components at baseline (participation in regional information meeting [y/n] and read newsletter [y/n]). The following patient-level-related baseline variables will be analysed and possibly adjusted for educational level, age, gender, co-morbidity, duration of pain, and earlier episodes of LBP.

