### Sample size

The control groups’ referral rate to secondary care is expected to be 18%. The intervention groups’ referral rate is expected to be reduced to 13%. Hence, this study is powered to detect a 5% point between groups difference in secondary care referral rates. Considerations of possible cluster effects led us to analyse possible intercorrelations. We analysed whether referral rates were the same between provider numbers in the North Denmark region in 2011. The data did not support any differences in referral rates between provider numbers. Assuming no cluster effect seemed unrealistic, and for that reason, a conservative estimate of a 16% cluster effect was used based on earlier studies on cluster effects in primary care [20]. Study size was estimated on an assumption of 90% power, a 5% level of significance, and a cluster effect of 16%. These assumptions lead to a requirement of 1,321 patients in each group. To allow for size difference between groups, the expected number of included patients was raised to 2,700 patients from 100 practices (Figure 1).

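### Pain, function and EQ-5D are planned as change from baseline with no named adjustment for the baseline score; an unadjusted change contrast would give up precision the collected data could supply

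*Protocol article*

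**What the plan says.** The protocol article's Secondary outcomes section sets the target: "Changes from baseline to four, eight, and 52 weeks are evaluated for the following secondary outcomes". The list that follows includes Roland Morris function, the 0 to 10 pain rating and EQ-5D.

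The Statistics section names the model for the continuous secondary outcomes: "practice number as a random effect in a linear mixed effects model with provider number as the intercept in profile analyses". It then lists patient-level baseline variables that will be examined and "possibly adjusted for educational level, age, gender, co-morbidity, duration of pain, and earlier episodes of LBP". The baseline value of the outcome is not in that list, nor among the practice-level variables listed just before it.

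The baseline score is available. Under Patient questionnaires, patients are asked to "fill in a questionnaire immediately after the initial GP consultation and after four, eight, and 52 weeks", and the section adds: "Included in the first questionnaire and repeated in the next three questionnaires are questions on the secondary outcomes".

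The article does not say whether the first score enters the profile model as a response, as a mean constrained to be equal across arms, or as a covariate.

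**The concern.** An unadjusted difference in change subtracts the whole baseline score, so it fixes the baseline coefficient at 1. With equal SDs, the regression of a later score on the first has slope r, the baseline-to-follow-up correlation, which is below 1. Subtracting too much adds noise. It also means that an arm which starts worse by chance appears to improve more, through regression to the mean alone.

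These outcomes carry the patient-outcome half of the trial's stated aim. Unnecessarily wide intervals, or estimates moved by a baseline difference, would weaken what the trial can say about that half. The primary outcome, 12-week referral, has no baseline score and is not touched.

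**Working it through.** **The plan's own figures.** The article states no SD, correlation, sample size or precision for any secondary outcome, so there is nothing to reproduce here. Its one sample-size figure, 1,321 per group, concerns referral. It is reproduced by 18% versus 13%, two-sided 5%, 90% power with continuity correction: 1,139 × 1.16 = 1,321. It has no bearing on this point.

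**Inputs.** From the article: change at 4, 8 and 52 weeks, 100 practices, 2,700 patients and about 80% questionnaire completeness. Assumed: r from 0.3 to 0.7, and equal SDs at baseline and follow-up.

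**Precision.** With a common SD σ:

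- variance of a change score: 2σ²(1 − r)
- variance with baseline as covariate: σ²(1 − r²)
- ratio, adjusted to change: (1 + r)/2, so the variance saved is (1 − r)/2
- SE ratio, change to adjusted: √[2/(1 + r)]

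| r | Change (σ² = 1) | Adjusted | Variance saved | SE larger under change | Carry-over of a 1-unit chance baseline difference |
|---|---|---|---|---|---|
| 0.3 | 1.40 | 0.91 | 35% | 24% | −0.7 |
| 0.5 | 1.00 | 0.75 | 25% | 15% | −0.5 |
| 0.7 | 0.60 | 0.51 | 15% | 8.5% | −0.3 |

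The last column is −(1 − r). At r = 0.8 and 0.9 the variance saved falls to 10% and 5%.

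**Unequal SDs.** Let k be the baseline SD divided by the follow-up SD. The change variance is then 1 + k² − 2rk (follow-up SD = 1) and the adjusted variance is still 1 − r².

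- k = 0.7: saving of 15%, 5% and 0% at r = 0.3, 0.5 and 0.7. For example, at r = 0.7, 1 + 0.49 − 0.98 = 0.51, the same as the adjusted variance.
- k = 1.3: saving of 52%, 46% and 41%.

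The range across these assumptions is therefore 0% to 52%.

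**Simulation with clustering.** The set-up was 50 practices per arm, 22 patients per practice (27 × 0.8 ≈ 22) and an assumed practice ICC of 0.05. The variance saved was 34%, 28% and 18% at r = 0.3, 0.5 and 0.7. The change contrast moved by −0.70, −0.56 and −0.32 per unit of chance baseline difference. The adjusted contrast moved by −0.01, −0.06 and −0.02. The formulas hold up.

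**In points.** Take an assumed Roland Morris SD of 5.5, ICC 0.05 (design effect 1 + 21 × 0.05 = 2.05), 50 × 22 = 1,100 patients per arm and r = 0.5. The SE of the change contrast is 5.5 × √(2 × 2.05/1,100) = 0.336. The adjusted SE is 0.336 × √0.75 = 0.291. The 95% half-widths are 1.96 × 0.336 = 0.66 and 1.96 × 0.291 = 0.57.

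**The case against.** **Exclusion of baseline is inferred from silence.** The adjuster list is tentative. Evaluating change does not rule out adjustment: change regressed on baseline gives the same arm effect as follow-up regressed on baseline. A profile model with a common baseline mean would recover about the same precision and fits the same words. This stands, so the point is conditional on the contrast being unadjusted. It does not remove the point. Target, model family and candidate covariates are all named, and the most useful covariate is missing from them.

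**The size rests on outside assumptions.** This also stands. The gain is modest on the raw scale, about a tenth of a Roland Morris point in half-width in the example above.

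**Recruitment after allocation.** A reader might infer that adjustment would also remove bias from unblinded GPs recruiting different patients in the two arms. The documents do not support that. The carry-over falls to about 0 only for chance imbalance. If recruitment produced a lasting 1-point severity difference with no true effect, the change contrast would be 0 and the adjusted contrast would be off by 1 − r: 0.7, 0.5 or 0.3 points.

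**The baseline form follows the first consultation.** In intervention practices the score may already reflect the GP's advice. This counts at least as much against a change score. Change subtracts all of any early effect, whereas adjustment subtracts a fraction r of it.

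**Missing first scores.** A mixed model with baseline as a response keeps a patient who lacks the first score, while a covariate model drops that patient unless the value is imputed. This stands and is dealt with in the fix.

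**Conclusion.** The point holds in conditional form. The article specifies change from baseline and does not name the outcome's baseline score among its adjusters, though it is collected. If the contrast is an unadjusted difference in change, then for r of 0.3 to 0.7 and equal SDs adjustment would cut the variance by 35% to 15%, and the planned SE is about 24% to 8% larger than it need be. Neither assumption is in the document, and with SD ratios of 0.7 to 1.3 the saving runs from 0% to 52%. A chance baseline difference carries over by (1 − r). That is not bias on average under randomisation; it is an error conditional on the imbalance observed.

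A reader might go further and conclude that the plan forbids baseline adjustment, or that a 15% to 35% loss is a property of this trial. The article says neither. This concerns secondary outcomes only, but the better method costs little and belongs in the plan before analysis.

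**What to change.** In the Statistics section, for Roland Morris, pain and EQ-5D:

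- Model the 4-, 8- and 52-week values with arm, time, arm-by-time and the patient's baseline score as a pre-specified, always-included covariate.
- Keep the practice random effect.
- Report the adjusted mean difference between arms at each time point, and align the Secondary outcomes wording with this.
- Keep patients with a missing first form or first score in the analysis, for example by simple imputation of the baseline covariate.
- Do not describe the adjustment as a remedy for differential recruitment after allocation. Because the first form follows the initial consultation, an unadjusted change analysis can be shown as a sensitivity analysis.

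The cost is a revision of the wording and some extra analysis work, including the handling of missing baseline scores. No new data or extra patients are needed, and the primary analysis does not change. Data collection was still running at publication and the analysts are to stay blinded until the analysis is complete, so the change could be fixed without knowledge of results.

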### Tertiary process outcomes

The following three areas will be described in relation to process evaluation: Did general practice receive the intended implementation activities? Did the intervention change the skills, beliefs, and behaviour of the GPs? Did the intervention change the beliefs and behaviour of the patient? The three areas are elaborated below.

### Evaluating the delivery of the implementation

Actual implementation delivered to interventions practices is monitored by the following items:

1. Delivered intervention at the initial guideline facilitator visit.

2. Use of STarT Back Tool and SOS questions.

3. Follow-up contacts with facilitators.

4. Use of data feedback by the GPs.

### Evaluating skills, beliefs and fidelity of the GP and guideline compliance

1. Skills are evaluated by asking about the GP’s satisfaction with own ability to handle LBP patients and if there are aspects that the GP wants to improve.

2. Beliefs of the GPs are evaluated by six questions on GP agreement with guideline recommendations. GPs are asked questions regarding patient history, patient examination, patient information, advice to stay active, and regarding referral to supplementary treatment in case the patient does not improve.

3. Behaviour of the GPs are evaluated by the referral rate in relation to the risk stratification (STarT Back Tool) and SOS questions, and the proportion of patients who have not improved by four weeks who have been advised to receive supplementary primary care treatment.

### Evaluating the beliefs and behaviour of the patient

Use of supplementary treatment, use of analgesics, and changes in Roland Morris Questions 9 and 23 in patient questionnaires will be used to evaluate changes in patient beliefs and behaviours. Changes will be measured eight weeks after the patient’s initial GP appointment.

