### Data collection

Collected data for this project will be kept and merged by an external provider using the unique personal identification number (CPR number) that is assigned to all Danish citizens. Data are collected from the guideline facilitators, pop-ups in the GPs electronic medical record (DAMD database), GP questionnaires, patient questionnaires, and regional registries (Figure 2).

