### Regional registries, facilitators, and GPs

Data regarding provider numbers and associated GPs will be delivered by the Primary Care Unit in the North Denmark region. The regional Department of Health Planning and Quality provide data on primary care reimbursements (*i.e.*, visits to GPs, physiotherapists, and chiropractors).

Following the initial visit and at later contacts with the intervention clinics, the guideline facilitator will log on to the project database and fill out a questionnaire to record which components of the intervention were delivered (Table 3).

**Table 3 T3:** Registrations from facilitators

**Topics at the initial guideline facilitator visit**	**Only intervention group practices**	
	**Answer**	**Appearance of textbox when answering no.**
Medical history	Yes/No	√
Clinical examination	Yes/No	√
Triage	Yes/No	√
ICPC-coding	Yes/No	√
Patient general advices	Yes/No	√
Re-evaluation	Yes/No	√
STarT Back Tool	Yes/No	√
SOcial Screening questions	Yes/No	√
Supplementary treatment	Yes/No	√
Referral to secondary care	Yes/No	√
Guideline hand-outs	Yes/No	√
Pop-up instructions	Yes/No	-
(If yes) – at the computer screen	Yes/No	-
Duration of visit	Minutes	-
Participants	Numbers	-
Follow-up appointment made	Yes/No	√

Overview of data collection from facilitator visits. The questions are entered into the database by the facilitator after the initial visit. Data concerning dates and topics in following contacts between facilitators and practices will be entered as well.

At inclusion and after six months, GPs are asked to fill out a questionnaire. They are asked about their capability, opportunity, and motivation for LBP treatment and their views on implementation strategies.

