### Ethics

The Regional Scientific Ethics Committee and the Danish Health and Medicines Authority did not find that any approval was necessary. The study was registered with the Danish Data Protection Agency, The Danish College of General Practitioners, and at ClinicalTrial.gov (registration number NCT01699256). Patients listed at the included practices are included without patient consent. Written informed consent from the patients for participating with questionnaires will be included in the first questionnaire. Patients may, at any time and without any consequence for their treatment, discontinue participation in the questionnaires. Other than filling out and leaving questionnaires, patients will not suffer any harm or inconvenience. Consent is sought from the participating GPs before the randomisation.

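### Use of supplementary treatment appears to rest on voluntary questionnaires alone, and the linked regional visit data that the trial already receives should be reported beside it

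*Protocol article*

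**What the plan says.** The section on evaluating the beliefs and behaviour of the patient gives the measures in one sentence: "Use of supplementary treatment, use of analgesics, and changes in Roland Morris Questions 9 and 23 in patient questionnaires will be used to evaluate" the changes of interest. It fixes the time point: "Changes will be measured eight weeks after the patient’s initial GP appointment". Patient questionnaires are the only source named there.

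The questionnaires are voluntary. Under Ethics, "Written informed consent from the patients for participating with questionnaires will be included in the first questionnaire", and under data completeness, "Data completeness from patient questionnaires (secondary outcomes) is expected to be about 80"%. Under recruitment of patients, the GP hands the envelope to patients who agree to be contacted. Under randomisation and blinding, the GPs know their allocation.

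Trial inclusion itself is not voluntary in this sense: "Patients listed at the included practices are included without patient consent". The section on regional registries says that a regional department will "provide data on primary care reimbursements", and physiotherapist and chiropractor visits are among them. The data collection section lists "GP questionnaires, patient questionnaires, and regional registries" among the sources and says that data are merged by personal identification number. None of the primary, secondary or tertiary outcome sections names the reimbursement data. The only regional data named there are the diagnoses used to check whether a referral led to secondary care.

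**The concern.** The Background describes primary care treatment as sufficient for most patients, with referral usually considered only after eight weeks without improvement. Whether more patients in the intervention arm took up physiotherapy or similar care is therefore a natural part of explaining any fall in referral. The GP behaviour outcome does not answer this, because it records whether treatment was advised and not whether it was used.

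If use is known only from questionnaires, it is known for a set formed after allocation in several steps: the patient agrees to be contacted, an unblinded GP hands out the envelope, the patient consents, and the patient answers at week eight. Each step could differ between arms, and the answer depends on recall. A difference between arms, or its absence, could then partly reflect who answered. A second source that avoids these steps is already being delivered and has no stated use in the article.

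**Working it through.** **The plan's own figure.** The article gives no sample size for this item. The only figure is 1,321 per group for referral. For 18% against 13%, two-sided 5% and 90% power, the two-proportion formula with continuity correction gives 1,139 per group, and 1,139 × 1.16 = 1,321. The figure reproduces, and the 16% cluster effect acts as a flat multiplier of 1.16.

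**Patients behind each source.** Inputs are 2,700 patients (Sample size) and about 80% completeness (data completeness section, denominator not stated). Consent shares are assumed.

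| Basis of the 80% | Patients | √(2,700 / patients) |
|---|---|---|
| All included patients | 2,700 × 0.80 = 2,160 | 1.12 |
| Consenters, 80% consent | 2,700 × 0.80 × 0.80 = 1,728 | 1.25 |
| Consenters, 60% consent | 2,700 × 0.60 × 0.80 = 1,296 | 1.44 |
| Consenters, 40% consent | 2,700 × 0.40 × 0.80 = 864 | 1.77 |

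The linked regional data could cover up to 2,700.

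**Precision.** The last column is the standard error relative to 2,700 patients, with equal prevalence and the same 1.16 multiplier at every size. At an assumed 50% use and 80% power, the detectable difference is (1.96 + 0.84) × √(2 × 0.25 × 1.16 / n per arm):
- 2,700 patients (n = 1,350): 5.8 points
- 2,160 patients (n = 1,080): 6.5 points
- 864 patients (n = 432): 10.3 points

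The flat multiplier favours the larger source. Suppose instead that 0.16 were an intra-practice correlation and losses were spread over all 100 practices. The design effect would be 1 + 26 × 0.16 = 5.16 at 27 patients per practice, 1 + 20.6 × 0.16 = 4.30 at 21.6, and 1 + 7.64 × 0.16 = 2.22 at 8.64. The standard error ratios would fall to √[(4.30 / 2,160) / (5.16 / 2,700)] = 1.02 and √[(2.22 / 864) / (5.16 / 2,700)] = 1.16. The precision gain therefore runs from slight to substantial, depending on clustering and consent.

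**Bias, for illustration only.** With 20% of an arm not answering, and non-responders' use differing from responders' by d points, that arm's observed proportion is off by 0.20 × d. For d of 5, 10 and 20 points the shift is 1, 2 and 4 points. It cancels in the comparison if both arms shift equally. The document gives nothing from which d, or its difference between arms, could be estimated.

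**What each source removes.** Linked visits avoid envelope hand-out, questionnaire consent, non-response and recall. They do not avoid selection at entry, because a patient enters the trial when an unblinded GP records a low back pain code.

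**The case against.** The strongest reply is that the section contains no error. The words about questionnaires may govern only the Roland Morris items, and the description of questionnaire content mentions advice received and followed but does not name use of supplementary treatment. Figure 2 maps measurements to data storage and could not be read here. The reimbursement data may be meant for the separate health economic protocol. The follow-up pop-ups already record applied supplementary treatment without needing questionnaire consent. The item is a tertiary process outcome, to be described and not formally tested.

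Much of this stands. The natural reading is still that questionnaires are the source. If the narrower reading is right, the item has no stated source, and one sentence is needed in either case. Use in an economic protocol would not prevent use here. The pop-up is a real further source, though it depends on the patient returning to the GP and on the GP's entry.

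A reader might infer that the questionnaire measure is more biased than a registry measure and should give way to it. The document does not support that. It describes supplementary treatment by examples that include exercises, and reimbursed visits miss home exercise and unreimbursed care. It does not restrict the visits to back pain, and unrelated visits may dilute a difference between arms even if equally common in both. Nor can the regional data supply analgesic use or the Roland Morris items. The two sources measure overlapping but different things, so the standard error ratios alone do not rank them.

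**Conclusion.** The point holds as a low-cost improvement to a tertiary process outcome. On the natural reading, use of supplementary treatment is known for at most about 2,160 of 2,700 patients, and for 864 to 1,728 if the 80% refers to consenters and consent is 40% to 80%. The set is formed after allocation with unblinded GPs involved. Linked visit data already in the trial could be reported beside it for up to all 2,700.

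This rests on two inferences. The first is that the regional data cover every included patient, which follows from linkage and from inclusion without consent but is not stated. The second is that they do not depend on questionnaire consent.

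Two stronger conclusions might be drawn and should not be. One is that the self-report has been shown to be biased: the route for bias is real, but its size and direction cannot be computed from the document. The other is that the process evaluation has no means of relating lower referral to primary care treatment: the pop-ups and the GP behaviour outcome give some information. The primary outcome, its power and the secondary outcomes are untouched.

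**What to change.** In the section on patient beliefs and behaviour:

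1. State which source defines the self-reported use of supplementary treatment, and report how many patients in each arm contribute.
2. Add, alongside it, the proportion of all included patients with any reimbursed physiotherapist or chiropractor visit within eight weeks of the first consultation. Compare it by allocated arm with allowance for practice clustering.
3. Report the pop-up record of applied supplementary treatment as a further comparator.
4. State the limits of the regional data: reimbursed visits only, not stated to be specific to back pain, home exercise not seen, and selection at the GP's diagnosis coding not removed.

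This mirrors the protocol's own check of GP-recorded referral against regional data. The cost is a few sentences and one added by-arm analysis of data already being delivered. Coverage of all included patients should be confirmed with the regional department first. The added proportion may also disagree with the self-report, and the report would then have to discuss that.
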